### Study population

#### Inclusion criteria

Between the ages of 18–24, inclusiveFluent in GermanPatient Health Questionnaire −9 (PHQ-9) score > 4

#### Exclusion criteria

History of epilepsyBDI Suicide Item = 3

##### Sample size

As this trial is primarily to establish feasibility, acceptability, and proof of concept, a full power analysis is not appropriate. However, to be able to assess feasibility process outcomes, we target recruitment at sixty participants (*n* = 60), with *n *= 40 receiving the intervention. There is no consensus on sample size of pilot studies – recommendations range from 12 [31] to 50 [32]. This sample size of *n* = 60 is in line with multiple best practice recommendations for feasibility trials and it is suggested that a sample of 30 in the intervention arm is sufficient for the main aims of this pilot study: to adequately establish feasibility and to interpret qualitative measures of acceptability [33, 34].

### Recruitment, screening and randomization

#### Recruitment, screening and randomization

All participants will be recruited from the community in Freiburg im Breisgau, Germany. Recruitment will be done via fliers placed around the city of Freiburg (i.e., on flier boards, on bicycles, etc.) and through the Max-Planck Institute’s MAXLab SONA system, which currently contains ~ 250 active participants. Fliers will be replenished around the city weekly and will include a QR code that will direct potential participants to the SONA system registration page. There, they will be directed to create an account and to take a screener questionnaire, consisting of the PHQ-9 and the BDI-II suicide item. If eligible for the study, they will immediately be directed to the online study consent form, from which they will be given a password to sign up for the first in-lab session on Qualtrics.

During the first in-lab session, participants will review the consent with the experimenter and then answer the baseline assessment battery. Following the completion of the baseline assessment, participants will be randomized to either the control condition or one of the treatment conditions. Randomization will follow a 1:1 allocation.

#### Participant timeline

A comprehensive overview of the study timeline and measure administration from screening through study completion is shown in the SPIRIT figure, Table 1.

#### Experimenter qualifications

The experimenter is a master’s level clinician who is fluent in English and German. Clinical experience and native language were prioritized when selecting an experimenter to ensure that the therapeutic elements of the study were delivered in a clinically and culturally appropriate way. The experimenter was trained by the first author on all elements of the study.

### VR equipment, environment, therapist and avatar design

#### Equipment

We will use a VIVE Pro headset to experience the VR. The experimenter will help participants adjust the headset and headphones to their comfort level. Participants will also be given controllers to interact with objects in the virtual environment. Prior to entering the VR, the experimenter will brief participants on the equipment and how to use it.

#### Environment

The virtual environment was developed using the Unity Pro engine (version 2017.3.1f1) and resembles a therapist’s office in an urban high-rise environment. The environment changes to reflect what the office looks like in the present day and what it will look like in 10 years from now. Participants will sit at a table with the therapist sitting at one end of the table and a large mirror on the other. See Fig. 3 for visuals of the virtual environment. Above the table is a virtual time machine (the existence and function of which will be explained by the therapist while the participant is in the VR). The room in the research lab where the experiment was conducted was decorated to resemble the office in the virtual environment (i.e., a similar rug, potted plants, books, etc.) to enhance the sense of realness once in the VR.

**Fig. 3 Fig3:**
[figure not shown]
The virtual environment

#### Virtual therapist

The virtual therapist avatar will be controlled by the experimenter and was designed in her likeness to enhance the sense of realness for participants once in the VR – see Fig. 4. The experimenter will be the same for all participants.

**Fig. 4 Fig4:**
[figure not shown]
A photo of the experimenter (**a**) alongside the avatar of the virtual therapist (**b**)

##### Participant avatars

Personalized virtual avatars will be created for each participant. These avatars are created with a photograph taken of the participant during the first session. Avatars of the participant’s present, one-week older, and 10-year older selves are created—see Fig. 5 for an example. Aged avatars were created using plug-in software that leverages an age-progression algorithm to create a 10-year older future self (developed by Change My Face; www.changemyface.com). The avatar body is adjusted to resemble the participant’s height and physique (Note: participants are seated while in VR, so the upper body is the only aspect that they will see). The shirt color is adjusted to match the color of the clothing the participant is wearing at the time they enter the VR. Participants are asked to choose colors for their future selves to wear.

**Fig. 5 Fig5:**
[figure not shown]
Example creation of participant avatars: Photo (left), Present Self (middle), 10-year-old self (right). The slide bar below the images allows for the adjustment of participant's aging

### Interventions

Three interventions will be administered. First, as a treatment as usual control (TAU), a Coping Plan is administered by the experimenter during the first in-person session to all participants. Next, participants in the treatment condition (TX) will all receive the Self-Help Intervention (SH) and the Positive Future Memories Intervention (PFM)—collectively known as the FutureU for Mental Health (FU-MH) Intervention. Participants in the TX condition will be assigned to either group A or B, which will dictate the order in which the SH and PFM interventions are received. Group A will first receive SH and then PFM; Group B will first receive PFM and then SH.

#### Coping plan intervention

The Coping Plan is an adaptation of Stanley and Brown’s [23] safety plan and is intended for use with people who struggle with regulating negative emotions but who do not report suicidal ideation [24]. The structure of the plan is the same as the Safety Plan but excludes the section on ‘Keeping the Environment Safe’. For participants who report suicidal ideation, the Safety Plan format (i.e., including ‘Keeping the Environment Safe’) will be used. The Coping Plan exercise will be informed by participants’ responses to the pre-questionnaire (specifically, the BDI-II and C-SSRS which measure depressive symptoms and suicidal ideation) and a follow-up conversation with the therapist about those responses. Participants will identify (a) Triggers and warning signs, (b) Things they can do to help themselves, (c) People or places that can distract them, (d) People they can talk to for help, (e) Professionals they can talk to for help, and (f) Things that make life worth living. A template for the coping plan can be found in Appendix 1.

#### FutureU for mental health intervention: self-help intervention

The goal of the self-help intervention is to practice coping skills and to improve self-efficacy around being able to help oneself in a moment of distress. The paradigm leveraged in this intervention is an adaptation of a self-compassion intervention developed by Falconer et al. in which participants encounter a crying child and deliver pre-rehearsed compassionate responses to the child as their current self [25]. They then embody the child and receive the compassion that they gave the child from the child’s perspective. In a pilot trial using this intervention with depressed patients, researchers found significant reductions in depression and self-criticism over a one-month period from baseline to follow-up [35].

In the self-help intervention, participants will meet with a virtual ‘therapist’ who will guide them through the exercise. In the first phase of the session, the participant will be told that they are about to meet their future self (FS) at a point 1 week into the future when they are experiencing a difficult moment. Participants are instructed to think about what that moment might be like—what their FS might be thinking or feeling (here, the therapist will reference the Triggers and Warning Signs that the participant came up with during the first session). The therapist tells the participant that they will leave the room and their FS will appear in front of them. The participant is instructed that they will need to speak to their FS to help them cope with the difficult moment. To begin speaking to their FS, participants will need to press a red button that is on the desk in front of them. They are instructed that this button will also record what they are saying. Participants will be told that they may (re)record their coping statements as many times as they like until they are satisfied. A digital copy of the coping plan will be available for the participant to reference during the exercise. As the participant delivers coping statements, the FS avatar—controlled by the experimenter—will become visually less distressed (facial expressions change from distressed to neutral after 2 statements and to slightly happy after 3 + statements) – see Fig. 6.

**Fig. 6 Fig6:**
[figure not shown]
Progression of 1-week-older future self from **a** distressed to **b** neutral to **c** happy as coping statements are given

In the second phase of the session, the participant will be told that they are now going to time travel 1 week into the future, to the exact moment in which they had just encountered their FS. This time, they will embody their FS and experience the moment through the eyes of their FS. Participants will be guided by the therapist to again try to imagine what they might be thinking and how they might be feeling at a moment when they have negative emotions. Once in the future, the participants will then listen to the recording of their own coping statements while looking at themselves in the mirror. Again, facial expressions will change from distressed to neutral to happy along with the delivery of coping statements. The participant will be given a recording of the coping statements and will be asked to listen to it at least one more time before the follow-up session. In addition, participants will be asked to reflect on what they learned from the session and how they might be able to apply it to their own lives.

#### FutureU for mental health intervention positive future memories intervention

The goal of the positive future memories intervention is to improve mood and future self-image by enhancing the valence and vividness of autobiographical future thought.

In this part of the intervention, participants will meet for a session with a ‘therapist’ in the VR environment. The therapist will be controlled by the experimenter and will guide the participant through the exercise. The participant and the therapist will both ‘time travel’ into the future and embody their future selves 10 years from the present day in a futuristic therapy office. The future therapist will then guide the participant through a series of embodiment exercises intended to enrich the participant’s perception of themselves in the future and to increase the general salience of the future-time perspective (see also [22]).

The participant and therapist will then return to the present day and debrief on how the session went and what it was like to hear about part of their future. The therapist will ask the participant to reflect on what they learned about themselves and how this exercise changed their perspective of themselves in the future. The participant will be given the image of themselves in the future as well as a recording of the conversation, which they will be asked to listen to at least one more time before the follow-up session. Participants are additionally asked to continue to reflect on their own about what they can take away from this experience.

### Outcomes measures

All measures taken during in-lab sessions will be conducted on a laptop in the lab space. All measures taken during follow-up and online control sessions will be self-administered by participants via link to a Qualtrics survey.

*Primary objective measures—feasibility and acceptability of the intervention*
Feasibility: Number of eligible participants, willingness of participants to fully participate
(i)Rates of recruitment into the studyNumber of potentially eligible participants on SONA systems.Number of participants who completed the PHQ-9 screener and BDI-II item.Number (and proportion) of participants who were eligible to participate.Number (and proportion) of participants who were ineligible to participate at screening and why.Number (and proportion) of participants who consented to participate in intervention.Number (and proportion) of participants who scheduled the first in-lab session.Number (and proportion) of participants who completed the first in-lab session.(ii)Retention to treatmentNumber (and proportion) of participants who successfully completed all parts of the intervention (sessions 1, 2, and 3).Number (and proportion) of participants who drop out of the study and, when freely shared, reasons for drop out. In accordance with our informed consent, participants are free to drop out of the study at any point without explanation.(iii)Completion of between session tasks(iv)Number (and proportion) of participants who report needing to use their Coping Plan.(v)Number (and proportion) of participants who report using their Coping Plan when needed.(vi)Number (and proportion) of participants who report listening to their Self-Help recording in the week following the intervention session and 3 months following the intervention session.(vii)Number (and proportion) of participants who report listening to their Positive Future Memories recording in the week following the intervention session and 3 months following the intervention session.(viii)Attrition at post-treatment follow-up pointsNumber (and proportion) of participants who complete the 1-week follow-up questionnaire.Number (and proportion) of participants who complete the 1-month follow-up questionnaire.(ix)Levels of missing clinical outcome dataProportion of data completion for each questionnaire at each time-point.

Feasibility: Adherence/Compliance rates—Rating and adherence to intervention protocol. See above for details.

Feasibility: Virtual Reality Engagement and Embodiment

(i)Embodiment in AvatarParticipants will complete a measure adapted from Banakou et al. 37 which assesses the degree to which participants experience the virtual avatar as their own body. The scale contains four items, each rated on a response scale of 1 = Strongly Disagree to 4 = Strongly Agree. Scores are determined by averaging responses to each item. Item three is reverse coded.(ii)Proteus EffectParticipants will complete a measure developed by van Gelder et al. 4 which assesses the degree to which people take over the characteristics associated with the avatar they embodied. The scale contains three items, each rated on a response scale of 1 = Strongly Disagree to 4 = Strongly Agree. Scores are determined by averaging responses to each item.(iii)PresenceParticipants will complete a measure adapted from Hartmann et al. 38 to assess the degree to which participants have the feeling they were actually present in the virtual environment, i.e., a shift in users’ self-location. The scale contains four items, each rated on a response scale of 1 = Strongly Disagree to 4 = Strongly Agree. Scores are determined by averaging responses to each item.(iv)EngagementParticipants will complete a measure adapted from O’Brien et al. 39 to assess the degree to which the participant feels engaged in the task in virtual reality. The scale contains fourteen items, each rated on a response scale of 1 = Strongly Disagree to 4 = Strongly Agree. Scores are determined by averaging responses to each item. Items 4, 5, and 6 are reverse coded.(v)Avatar RecognitionParticipants will complete a measure developed by van Gelder et al. 40 which assesses the degree to which participants can identify and recognize themselves in the avatar of their future self. The scale contains seven items, each rated on a scale of 1 = Strongly Disagree to 7 = Strongly Agree. Scores are determined by averaging responses to each item.

Acceptability-Feasibility: Assessment of Intervention (Acceptability of Intervention Measure—AIM; Intervention of Appropriateness Measure—IAM; Feasibility of Intervention Measure—FIM)—The AIM, IAM, and FIM are self-report measures of outcomes associated with implementation success [41]. The scales can be modified to reflect the type of service being implemented. Each scale contains four items which are rated on a response scale of 1 = Completely Disagree to 5 = Completely Agree. Scores are obtained by averaging responses for each measure. No items are reverse coded. Each scale has demonstrated strong validity and reliability [42].

Acceptability: Participant Satisfaction and general feedback—participants will respond to a brief survey assessing their satisfaction with the intervention and eliciting any feedback about the exercises. This survey was developed by the investigators for the purpose of this study.

2.
*Secondary objective measures – Establishing a proof of concept for the intervention*
Demonstrating the intended effect on the targeted cognitive mechanisms.
(i)*Improvement in Quality of Thoughts of the Future Self –* Participants will respond to two measures assessing thoughts of the future self:First, a scale developed by van Gelder et al. [40] contains 5 items assessing the vividness of the future self. This scale asks participants to indicate the extent to which they agree with how clearly and easily they can describe or imagine themselves in the future. These items are on a scale of 1 = Strongly Agree to 7 = Strongly Disagree.For valence, a single-item pictorial assessment developed by Bradley and Lang [43] asks participants to select which of five emotional expressions ranging from sad to happy best represent how they feel about themselves 10 years in the future.For relatedness, two single-item pictorial assessments adapted from a task developed by Ersner-Hershfield et al. [44] which ask participants to select a pair of Euler circles which represent the extent of their feelings of connection or similarity between their present and future selves. Participants are presented with seven options ranging from completely separate circles to completely overlapping circles.Collectively, the vividness, valence, and relatedness items have been used to assess the broader construct of Future Self Identity [45].Next, a separate scale measuring the same construct, the Future Self Continuity Scale developed by Sokol and Serper [46], assesses the similarity, vividness, and positive affect for the future self. This scale contains four items related to similarity, three items related to vividness, and three items related to positive affect. Each item is rated on a scale of 1 = Not at all to 6 = Perfectly. Total and subscale scores are obtained by averaging items overall and in the respective subgroups.
Valence:Improvement in the valence of thoughts of the future self (i.e., thoughts becoming more positive) among participants in the treatment condition from pre-to-post intervention.A larger improvement in the valence of thoughts of the future self among participants in the treatment condition versus participants in the control condition from baseline to each measurement point post-intervention.VividnessImprovement in the vividness of thoughts of the future self (i.e., the mental image becoming clearer and more detailed) among participants in the treatment condition from pre-to-post intervention.A larger improvement in the vividness of thoughts of the future self among participants in the treatment condition versus participants in the control condition from baseline to each measurement point post-intervention.RelatednessImprovement in the sense of connection to the future self among participants in the treatment condition from pre-to-post intervention.A larger improvement in the sense of connection to the future self among participants in the treatment condition versus participants in the control condition from baseline to each measurement point post-intervention.Improvement in the sense of similarity to the future self among participants in the treatment condition from pre-to-post intervention.A larger improvement in the sense of similarity to the future self among participants in the treatment condition versus participants in the control condition from baseline to each measurement point post-intervention.
(ii)Improvement in quality of future thoughts—Participants will complete the Prospective Imagery Task (PIT) at the baseline and final assessments [47]. The PIT asks participants to generate a mental image in response to 10 negative future scenarios and 10 positive future scenarios and indicate how vivid each image is on a scale from 1 = no image at all to 5 = very vivid.Improvement in the vividness of future thoughts among participants in the treatment condition from baseline to 3-months post-intervention follow-up.A larger improvement in the vividness of future thoughts among participants in the treatment condition versus participants in the control condition from baseline to 3-months follow-up.

*Demonstrating evidence of improvement in clinical outcomes*

(i)Improvement in symptoms of depression—Participants will respond to the Beck Depression Inventory—II (BDI-II) at baseline and at the 3-month follow-up session [48]. The BDI-II is the most widely used measure of depressive symptoms and has demonstrated good reliability and validity in clinical and nonclinical German samples [49]. The scale is comprised of 21 items assessing the presence and severity of depressive symptoms. Each item includes 4 response options ranging from no experience of symptoms to severe experience of symptoms; for example, 0 – *I do not feel sad* to 3 – *I am so sad or unhappy that I can’t stand it*. Scores are obtained by summing total items and range from 0 to 63. Total scores from 0 to 13 indicate minimal depression, 14 to 19 mild depression, 20 to 28 moderate depression, and 29 to 63 severe depression.Improvement in reported symptoms of depression among participants in the treatment condition from baseline to 3-months post-intervention follow-up.A larger improvement in reported symptoms of depression among participants in the treatment condition versus participants in the control condition from baseline to 3-months follow-up.(ii)Reduction in frequency and severity of suicidal ideation – Participants will respond to the German language validated Columbia – Suicide Severity Rating Scale adapted for use in Research [50] at baseline, each pre-intervention questionnaire, and the 1-week and 3-month follow-up. Based on responses, participant scores will be categorized as low, moderate, or high risk.Improvement in reported frequency and severity of suicidal ideation among participants in the treatment condition from baseline to each measurement occurring post-intervention (i.e., session 3 pre-intervention, 1-week follow up, 3-month follow up).A larger improvement in reported frequency and severity of suicidal ideation among participants in the treatment condition versus participants in the control condition from baseline to each measurement occurring post-intervention (i.e., session 3 pre-intervention, 1-week follow up, 3-month follow up).(iii)Reduction of negative affect, Improvement in Positive Affect—Participants will respond to the German language validated Positive and Negative Affect Scale (PANAS) at every measurement point [51]. The PANAS is made up of two 10-item scales measuring positive and negative affect. Each item is rated on a scale from 1 = Very Slightly, or Not at all to 5 = Extremely. Scores are obtained by averaging responses to items within the positive and negative subscales.Improvement in affect, i.e., increase in positive affect and decrease in negative affect, among participants in the treatment group from pre-to-post intervention and from baseline to 1-week and 3-month follow-up.A larger improvement in affect among participants in the treatment condition versus participants in the control condition from baseline to each measurement occurring post-intervention.(iv)Improvement in self-efficacy—Participants will respond to the German language validated General Self Efficacy Scale (GSES) at baseline and 3-month follow-up [52]. The scale has 10 items assessing participants’ overall sense of self-efficacy with dealing with difficulties. Items are rated on a scale from 1 = Completely Disagree to 4 = Completely Agree. Scores are obtained by averaging scores across all items.Improvement in self-efficacy among participants in the treatment condition from baseline to 3-month follow-up.A larger improvement in self-efficacy among participants in the treatment condition versus participants in the control condition from baseline to 3-month follow-up.

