### Analyses

#### Primary objective—feasibility and acceptability of the intervention

As outlined in the outcomes section, descriptive data on the feasibility and acceptability of the intervention will be provided. Descriptive statistics will be reported for continuous and pseudo-continuous variables assessing each individual part of the intervention, i.e., for the SH and PFM interventions. Frequencies will be reported for categorical data.

Participant’s progress through the trial will be reported in a CONSORT diagram*—*see Fig. 7. This will indicate the number of participants who were eligible, consented, began, and completed the study, as well as the number of participants who dropped out, at which timepoint, and why (if reason is known).

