#### Secondary objective—establishing a proof of concept for the intervention

Assessment of change in targeted cognitive mechanisms and clinical outcomes will be completed as is outlined in the outcomes section. Due to the modest sample size, these analyses will be completed to pilot the method for a full-scale RCT and to explore trends. The significance of effects will be interpreted and discussed within the context of the statistical limitations of a pilot trial.

Between-group differences for participants in the treatment condition versus the control condition will be assessed using independent-sample *t*-tests. Here, interpretation of Cohen’s *d *will be done using between-group standard deviations. The significance of between-subject changes will also be assessed through calculation of a reliable change index (RCI) [53] and evaluation of confidence intervals for mean differences.

Between-group differences in the targeted cognitive mechanisms and clinical outcomes will additionally be assessed through Latent Growth Curve Modeling (LGCM). This analysis will allow us to evaluate the difference in trajectories of change in cognitive mechanisms and clinical outcomes between the control and treatment conditions. The hypothesized changes in thought processes and subsequent clinical outcomes are expected to continue to grow over time post-intervention, rather than improve wholly and discretely at the point of intervention. The LGCM approach will allow us to observe whether this growth hypothesis is borne out.

For all analyses, age and gender will be included as covariates. Gender is included for the potential biasing effect on reports of depression. Cross-nationally, women endorse depression at highly elevated rates versus men [54]. Age is included for the potential biasing effects on future-oriented thinking. The future is conceived differently at different stages of life. Although variation in stages of life is comparatively low given the already constricted age range (18–24), there are still some meaningful differences in life stage that may impact future perspective when comparing an 18 versus 24-year-old.

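### Suicidal ideation is named as frequency and severity, but the only C-SSRS score defined is a three-level risk category, and the planned analyses do not fit it

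*Protocol article*

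**What the plan says.** In the protocol article, Outcomes measures, the second clinical outcome is headed "Reduction in frequency and severity of suicidal ideation". Its between-group target is worded the same way: "A larger improvement in reported frequency and severity of suicidal ideation among participants in the treatment condition versus participants in the control condition", from baseline to the session 3 pre-intervention, 1-week and 3-month assessments. The one sentence on scoring is "Based on responses, participant scores will be categorized as low, moderate, or high risk". The BDI-II, the PANAS and the self-efficacy scale, in the same list, each get a numeric score (a sum or a mean).

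The analysis section for the secondary objective opens with "Assessment of change in targeted cognitive mechanisms and clinical outcomes will be completed as is outlined in the outcomes section". It continues: "Between-group differences for participants in the treatment condition versus the control condition will be assessed using independent-sample" t-tests, with Cohen's d. It adds "calculation of a reliable change index (RCI) [53] and evaluation of confidence intervals for mean differences", and says that group differences in mechanisms and "clinical outcomes will additionally be assessed through Latent Growth Curve Modeling (LGCM"). No separate method is given for an ordinal outcome. The sentence "Frequencies will be reported for categorical data" stands under the primary, feasibility objective.

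**The concern.** The article fixes a scoring rule for this outcome, and the rule does not measure what the outcome is called. A risk category is neither a frequency nor a severity score. Cohen's d, the RCI and mean differences all presuppose a numeric scale, which low, moderate and high do not supply.

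Two readings are open. Either the category is analysed, and information in the responses is thrown away, or some other C-SSRS score is analysed and the article does not define it. Both need the same repair.

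Suicidal ideation is in the trial's title and hypotheses, and the secondary analyses are meant to pilot the method for a full-scale trial. An unsuitable score would be carried forward into that trial.

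**Working it through.** The protocol gives no power, effect size or baseline distribution for this outcome, so there is no figure to reproduce. The check has three steps.

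**1. Outcome, score and method side by side**

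| Outcome | Score defined | Fits t-test, Cohen's d, RCI? |
|---|---|---|
| BDI-II | Sum, 0 to 63 | Yes |
| PANAS | Subscale means | Yes |
| Self-efficacy | Mean of 10 items | Yes |
| Suicidal ideation | Low / moderate / high risk | No numeric score |

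**2. Who could show improvement on the category**

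Entry needs a PHQ-9 score above 4 and no minimum ideation (Inclusion criteria). A BDI suicide item of 3 is excluded (Exclusion criteria). Both push the sample towards the lower end. The share starting in the lowest level is not given, so it is varied here. Number able to improve = 60 × (1 − share in lowest level):

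- 33%: 40
- 50%: 30
- 70%: 18
- 80%: 12
- 90%: 6

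**3. Cost of the three-level cut**

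From the protocol: 60 participants, 40 of them treated, so 20 controls. Assumed: a 0-5 severity score with control percentages 40/22/16/12/6/4, a treatment effect acting as a common odds ratio (OR), a two-sided 5% test, and two groupings (0-1 / 2-3 / 4-5 and 0-2 / 3 / 4-5).

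Treated cumulative probability = OR × odds / (1 + OR × odds), where odds = F / (1 − F) and F is the control cumulative probability. For OR 3:

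- Scores 0-1: F = 0.62, odds 1.632, × 3 = 4.895, treated 0.83.
- Scores 0-2: F = 0.78, odds 3.545, × 3 = 10.636, treated 0.91.

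So 62% or 78% of controls, and 83% or 91% of treated participants, fall in the bottom category. Simulated power (3,000 replicates, single follow-up score):

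| | Rank test | t-test |
|---|---|---|
| OR 3, full 0-5 score | 56% | 53% |
| OR 3, grouping 0-1 / 2-3 / 4-5 | 44% | 43% |
| OR 3, grouping 0-2 / 3 / 4-5 | 29% | 30% |
| OR 4, full 0-5 score | 74% | 71% |
| OR 4, grouping 0-1 / 2-3 / 4-5 | 61% | 59% |
| OR 4, grouping 0-2 / 3 / 4-5 | 41% | 42% |

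With no effect, the t-test rejects in 4.3-5.5% of trials. Reading across a row, the choice of test moves power by at most 3 points. Reading down at OR 3, the cut removes 10 to 27 points.

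A second model works on change from baseline, which is closer to the stated target. It uses a latent normal score, baseline to follow-up correlation 0.5, a 0.8 SD shift, and a t-test on change, 40 versus 20. Power on the full score is 0.82. On three levels it is 0.61, 0.50, 0.33, 0.24 and 0.14 when 33%, 50%, 70%, 80% and 90% start in the lowest level.

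**The case against.** A reader might infer that the protocol compares the risk category by t-test, so that frequency and severity are not analysed at all. The text does not say so. The targets straight after the scoring sentence are still worded as frequency and severity, and the analysis section refers back to them. A condensed article may also leave the exact model variable to a fuller document. This stands against the strong reading. It does not remove the mismatch, because the article does state a scoring rule, states only that one, and names no method that suits it.

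A reader might also infer that most improvement cannot register. That needs a baseline distribution and cut-offs, and neither is given. In the second model it is true when well over half start in the lowest level. It is borderline near 50%, and false when the levels are evenly filled (51-61% of treated improvers then change category, over correlations of 0.5 and 0.7). Nor does the article say where people without ideation are placed. That they share the lowest level with mild ideation is an assumption, and the Coping Plan section shows that the study does tell the two apart.

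Nor is the t-test invalid: its error rate holds at about 5%. The growth curve cannot be faulted for being linear, because no form is specified.

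Finally, the outcome is one of several secondary ones. The section calls these analyses a pilot of the method and a look at trends, and the progression criteria rest on feasibility and acceptability. This stands, and it limits the weight of the point.

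**Conclusion.** The point holds in a limited form. The named outcome and the only defined score do not match, and Cohen's d and the RCI are assigned without a numeric score to carry them. If the category is analysed, change within a level is lost, and participants in the lowest level at baseline can only stay or worsen.

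Under the assumed 0-5 distribution and an odds ratio of 3, power falls from about 53-56% to about 30-45%, the range over the two groupings and repeated runs. The size depends wholly on the assumed distribution, groupings and effect; the direction does not. The trial is not powered for clinical outcomes, so these figures show how much information is lost and do not set a target that the trial misses. No progression decision depends on this comparison. The repair is worth making because the method is being piloted for a larger trial.

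**What to change.** - Keep the low / moderate / high category for safety reporting only.
- Name the analysed variable as the uncut C-SSRS ideation severity level, with no ideation as its lowest value. Compare arms with a baseline-adjusted ordinal model or a rank-based method.
- Report the proportion with any ideation by arm and time point.
- Analyse frequency or intensity only at time points where it is collected from everyone who reports ideation; otherwise drop frequency from the outcome name. The safety protocol has the experimenter go through the intensity questions with those who report ideation, while follow-ups and online control sessions are self-administered. The article therefore does not establish that these items exist at every point.
- Do not apply Cohen's d or the RCI to the category.

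**Cost.** For severity this is a change of analysis wording, since Table 1 already schedules the C-SSRS at five time points. For frequency, what is collected online must be checked first. The effect measure becomes an odds ratio or a rank measure in place of Cohen's d. With 20 controls, and age and gender already planned as covariates, an ordinal model may meet sparse cells. The rank-based comparison should then be the stated fallback.
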